### Pregnancy Test

For women with reproductive potential: Serum or urine  $\beta$ -HCG (urine test must have a sensitivity of 25-50 mIU/mL) must be performed at each safety evaluation time point, and/or whenever pregnancy is suspected.

#### Fasting lipids, Glucose, Insulin, hsCRP

Total cholesterol, HDL cholesterol, LDL cholesterol (direct), triglycerides, hsCRP, and glucose will be performed at entry and weeks 12 and 24 in real time at the local laboratory. Insulin will be batched and analyzed at the end of the study.

#### Plasma HIV-1 RNA

HIV-1 RNA must be performed by a laboratory that possesses a CLIA certification or equivalent. Eligibility will be determined based on a screening value of <50 copies/mL.

#### CD4+ Count

Obtain absolute CD4+/CD8+ counts and percentages. All laboratories must possess a CLIA certification or equivalent.

#### Safety Labs

CBC with differential, chemistry panel including liver enzymes (ALT, AST, Alk Phos), total bilirubin, serum creatinine, and urine or serum pregnancy test. All safety labs, HIV-1 RNA, and CD4 cell counts will be done at local certified laboratories.

#### Fasting Stored Serum, Plasma and Urine

If subjects come to the appointment and are not fasting, they will need to come back in fasting state for these evaluations within a 7-day window.

Serum (3 mL), plasma (3 mL), and clean-catch urine (minimum of two and maximum of six 3 mL aliquots. Please see Manual of Operations for further details) should be collected for storage as indicated in the schedule of events (entry, Week 12, Week 24). An additional set of banked samples (identical in volume to above) should be collected in the event of study discontinuation. Frozen specimens will be collected, labeled with patients' PID and date of draw, and stored in a –70 degrees freezer (urine specimens may be refrigerated up to 24 hours prior to freezing if needed) until analyses can be performed. The stored samples will be used for future measurements of markers of inflammation and glucose/lipid regulation such as CRP, TNF- $\alpha$ , soluble TNF receptors I and II, IL-6, adiponectin, leptin, insulin, HOMA-IR, myeloperoxidase (MPO), prostaglandin metabolites.

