## 6.0 CLINICAL EVALUATIONS

### 6.1 Schedule of Events

|                                                                                 | Screen | Baseline* | Week 1 | Week 2 | Week 6 | Week 12* | Week 18 | Week 24* |
|---------------------------------------------------------------------------------|--------|-----------|--------|--------|--------|----------|---------|----------|
| Informed Consent, Patient's Bill of Rights, HIPPA, medical information release  | X      |           |        |        |        |          |         |          |
| Targeted physical exam with weight, blood pressure                              |        | X         | X      | X      | X      | X        | X       | X        |
| Complete physical exam and height                                               | X      |           |        |        |        |          |         |          |
| CT- L4/5                                                                        |        | X         |        |        |        |          |         | X        |
| Mid-waist, hip and neck circumferences and waist/hip ratio                      | X      | X         |        |        |        |          |         | X        |
| HIV-1 RNA                                                                       | X      | X         |        |        |        |          |         | X        |
| Safety labs**                                                                   | X      | X         |        |        | X      | X        | X       | X        |
| CD4 cell counts                                                                 |        | X         |        |        |        |          |         | X        |
| Fasting lipids, hsCRP, banked serum and plasma                                  |        | X         |        |        |        | X        |         | X        |
| Urine samples for markers of oxidant stress and endothelial activation, protein |        | X         |        |        |        | X        |         | X        |

\* Entry, week 12, and week 24 laboratory evaluations are required to be fasting (at least 8 hours).

\*\*Safety labs include: CBC with differential, chemistry panel [including liver enzymes (ALT, AST, Alk Phos) and total bilirubin, serum creatinine], urine or serum pregnancy test. All safety labs, HIV-1 RNA, and CD4 cell counts will be done at local certified laboratories.

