### **Visit 2 Baseline (Week 0, within 30 days of screening)**

Once eligibility has been confirmed, the subject will be scheduled for baseline evaluation, which includes safety lab evaluation and the collection of stored serum, plasma, and urine samples for future analyses. Telmisartan 40 mg po daily will be distributed at this evaluation, and the subject will be counseled (again) regarding adherence and potential medication side effects.

For all subsequent visits, evaluations should be performed +/- 14 days from the expected date. Medication adherence/compliance and method of birth control (if applicable) will be assessed and documented at every visit.

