## **6.6. Laboratory Evaluations**

Fasting will be required for study entry, Week 12, and Week 24. Fasting will be defined as nothing by mouth except water and medications for at least 8 hours prior to the lab draw. At screening and entry, all laboratory values must be recorded on the CRFs regardless of grade. For post-entry assessments, record all laboratory values  $\geq$  Grade 2. Any laboratory value that led to a change in study treatment (telmisartan), regardless of grade, must be recorded. Fasting lab studies include: total cholesterol, LDL cholesterol, triglycerides, HDL cholesterol, glucose, and insulin.

**Sites must refer to the Division of AIDS Table for Grading the Severity of Adult and Pediatric Adverse Events** (see Manual of Operations), **Version 1.0, December 2004, to establish grading.**

The table is available on the telmisartan study website at  
<http://www.uclacarecenter.org/MATHtrial.org>.

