### **9.3 Primary Endpoint Assessments**

VAT volume (cm^2) will be calculated from a single 5 mm slice CT scan obtained at the level of the L4-L5 inter-vertebral disc space. CT scans will be obtained prior to telmisartan initiation and at study termination (Weeks 0 and 24). All CT scans will be standardized and communicated via electronic medium (CD, DVD, or optic disk) to the central reading center at Tufts University. The central reader will be blinded to patient characteristics.

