### **9.4 Secondary Endpoint Assessments (Change in below calculated between Weeks 0 and 24)**

- Abdominal SAT and VAT:SAT ratio, as calculated from single slice CT scan (as above)
- Total cholesterol, HDL cholesterol, triglycerides, LDL cholesterol (direct)
- Markers of inflammation

- Insulin, glucose, HOMA-IR
- Framingham Risk Score calculation
- Prevalence of metabolic syndrome
- Systolic and diastolic blood pressure measurements
- Urinary protein excretion and serum creatinine measurement

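### The protocol allows a non-fasting subject's entry fasting samples to be drawn up to 7 days after telmisartan is handed out, so some stored-sample Week 0 values may be on drug

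*Protocol*

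**What the plan says.** All references are to the Protocol.

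- **Section 6.2, Visit 2 Baseline.** The baseline evaluation is one "which includes safety lab evaluation and the collection of stored serum, plasma, and urine samples for future analyses". The next sentence says: "Telmisartan 40 mg po daily will be distributed at this evaluation". Dispensing is not made conditional on the samples having been drawn.
- **Section 6.1, note to the Schedule of Events.** "Entry, week 12, and week 24 laboratory evaluations are required to be fasting (at least 8 hours").
- **Section 6.6, opening paragraph.** "Fasting will be defined as nothing by mouth except water and medications for at least 8 hours prior to the lab draw". The paragraph goes on: "Fasting lab studies include: total cholesterol, LDL cholesterol, triglycerides, HDL cholesterol, glucose, and insulin".
- **Section 6.6, Fasting Stored Serum, Plasma and Urine.** Subjects who turn up without having fasted are told that "they will need to come back in fasting state for these evaluations within a 7-day window". The paragraph that follows names entry, Week 12 and Week 24 as the collection points, with no exception for entry.
- **Section 9.3.** For the primary endpoint, "CT scans will be obtained prior to telmisartan initiation".
- **Section 9.4.** The secondary endpoints are listed under the rule "Change in below calculated between Weeks 0 and 24".

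**The concern.** The trial has a single arm (Sections 3.0 and 9.2), so the Week 0 value is the only reference against which a laboratory change is judged. If that value is taken after a few days of telmisartan, any effect already present is subtracted from the result.

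This would happen only in subjects who came to Baseline without fasting, so the affected baselines would not be a random subset. For the stored samples, Section 6.1 schedules no collection before Baseline, so there is no earlier sample to fall back on for those subjects.

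**Working it through.** **1. Can a site follow every sentence and still obtain an on-drug Week 0 sample?**

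- Section 6.2 hands out the drug at the Baseline visit without a condition.
- Section 6.6 lets the entry samples of a non-fasting subject come up to 7 days later and does not say to hold the drug.
- The fasting definition in Section 6.6 permits medications, so a telmisartan dose before the return draw does not breach it.
- Section 6.2 places Visit 3 at 7 days after telmisartan is started, so the return draw can fall as late as that visit.
- Only the CT scan carries a pre-drug requirement (Section 9.3).

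So yes: the text permits it, although it does not direct it.

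**2. Why entry and not Weeks 12 and 24?** Section 6.2 already gives all visits after Baseline a window of 14 days either side. A 7-day return adds little there. At entry it can move the draw across the start of treatment.

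**3. Which endpoints are exposed?**

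| Endpoint in Section 9.4 | Exposure |
|---|---|
| Inflammation markers from stored samples; insulin, hence HOMA-IR; urinary markers | Direct: the return rule sits under the stored-sample heading |
| Lipids, glucose, hsCRP (real-time, local laboratory) | By inference only, from the fasting requirement in Sections 6.1 and 6.6 |
| Framingham score, metabolic syndrome | By the same inference, through lipid or glucose components |
| Serum creatinine | Less clear: a safety laboratory test, also drawn at screening |
| SAT, VAT:SAT (and the primary VAT) | None: protected by Section 9.3 |

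**4. How large could the effect be?** The plan gives no figure for this, so there is none to reproduce. Its sample size of 27 concerns VAT and is untouched.

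Let *f* be the share of subjects whose Week 0 sample is drawn on drug, and *g* the share of the 24-week effect already present at that draw. With a true mean change Δ, affected subjects show Δ(1 − g) and the others Δ. The observed mean is

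(1 − f)Δ + fΔ(1 − g) = Δ(1 − f·g),

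so the mean change shrinks by f·g.

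Neither input is in the documents. Assumed ranges:

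- f = 10% to 20%, which is 35 × 0.10 = 3.5 to 35 × 0.20 = 7 subjects.
- g from 4.2% (an effect accruing evenly over 24 weeks: 7/168 = 0.042) to 80% (a fast-responding marker).

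| f | g | Shrinkage f·g |
|---|---|---|
| 10% | 4.2% | 0.4% |
| 20% | 4.2% | 0.8% |
| 10% | 30% | 3% |
| 20% | 50% | 10% |
| 20% | 80% | 16% |

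A higher *f* with a moderate *g* gives a similar upper figure: 0.30 × 0.50 = 15%. All rows put the late draw at the full 7 days. The table illustrates the dependence on the inputs and is not a bound.

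**The case against.** The strongest reply is that a consistent reading exists in which nothing goes wrong. Section 6.2 lists sample collection as part of the baseline evaluation and mentions dispensing afterwards. Section 6.1 requires entry laboratory work to be fasting, so a site may treat Baseline as unfinished, and dispense nothing, until the samples are in. Handing out tablets is also not the same as taking the first dose. Section 6.2 times Visits 3 and 4 from the start of telmisartan rather than from the Baseline visit. Section 6.4 foresees Week 0 data in subjects who never start treatment.

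That reading is open, but no sentence requires it. The passages on Visits 3 and 4 and on non-starters are compatible with a pre-drug baseline without imposing one. What the reply does establish is that a reader may not infer that the protocol instructs sites to dose before sampling.

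Three other stronger readings also fail:

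- **That most laboratory endpoints are affected.** The 7-day rule stands under the stored-sample heading. Lipids, glucose and hsCRP come in only by inference.
- **That the damage would be invisible or beyond any remedy.** Section 6.6 has specimens labelled with the date of draw, so late samples could be identified against the first-dose date and excluded or examined separately. The individual's pre-drug value would still be lost.
- **That a particular dilution is established.** Both inputs are assumed, and with slow accrual the effect is below 1%.

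It is also fair to say that the endpoints concerned are secondary, and that Section 9.6 declares the analysis exploratory.

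**Conclusion.** The point holds as a gap between two stated rules. Sections 6.2 and 6.6 together allow, but do not direct, an entry stored sample to be taken on drug up to 7 days after Baseline, and only CT is protected. The exposure is direct for inflammation markers, insulin and HOMA-IR, and urinary markers. It is inferential for real-time lipids, glucose and hsCRP, and absent for VAT, SAT and VAT:SAT.

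If the drug acts early, the change in the affected subjects would tend to be biased toward zero. The documents do not allow the size to be stated. Under the assumed rates above it lies between about 0.4% and 16% of the mean change. This does not threaten the primary result. It is worth correcting because the secondary comparisons have no reference other than Week 0 and the correction is nearly free.

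**What to change.** Reconcile Section 6.2 (Visit 2 Baseline) with Section 6.6 (Fasting Stored Serum, Plasma and Urine) in two sentences:

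1. Define the Week 0 fasting blood and urine as samples obtained before telmisartan initiation, in line with what Section 9.3 already requires for CT.
2. State that a sample drawn after the first dose is not used as a Week 0 value in the change analyses. This needs the first-dose date to be available alongside the draw date.

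How dispensing and the first dose are arranged around a return visit is for the sponsor and investigator to settle; this point concerns only which samples count as baseline.

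The cost is a possible short delay, or a few missing baseline values, among subjects who arrive non-fasting. No new procedure is needed.

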### **7.0 TOXICITY MANAGEMENT**

Criteria for subject management and dose interruptions, modifications, or discontinuation will pertain only to toxicities attributable to telmisartan. Toxicities due to drugs in the background regimen should be managed according to standard clinical practice, with the goal of maintaining continuous therapy, if possible.

#### **7.1. Grade 1 or 2 Toxicity**

Subjects who develop a Grade 1 or 2 AE or toxicity may continue telmisartan.

#### **7.2 Grade 3 Toxicity**

Subjects who develop a Grade 3 AE or toxicity should have telmisartan withheld unless the investigator has compelling evidence that the AE was not caused by telmisartan. The study chairs

(Drs. [name] or [name]) should be notified of any Grade 3 or greater toxicity. The subject should be re-evaluated closely until the AE returns to Grade  $\leq 2$ , at which time telmisartan may be reintroduced at the discretion of the site investigator or according to standard practice.

If the same Grade 3 AE recurs within 4 weeks and it is thought to be related possibly, probably, or definitely to telmisartan, then telmisartan must be permanently discontinued. If the same Grade 3 AE recurs after 4 weeks but is not thought to be related to telmisartan, the management scheme outlined above may be repeated.

Subjects experiencing Grade 3 or greater AEs (requiring permanent discontinuation of telmisartan) should be followed closely for resolution of the AE to Grade  $\leq 2$ , and the study chairs must be consulted.

Subjects with Grade 3 asymptomatic laboratory abnormalities in cholesterol or triglycerides may continue telmisartan. Grade 3 asymptomatic elevations of bilirubin in subjects on atazanavir therapy will also be permitted.

### **7.3 Grade 4 Toxicity**

Subjects who develop a Grade 4 symptomatic AE or toxicity will have telmisartan discontinued. If the site investigator has compelling evidence that the AE has not been caused by telmisartan, dosing may resume when the AE has resolved and after consulting with the study chairs. Subjects experiencing Grade 4 AEs requiring permanent discontinuation of telmisartan should be followed closely until resolution of the AE to Grade  $\leq 2$ , and the study team must be consulted.

Subjects with Grade 4 asymptomatic laboratory abnormalities in cholesterol or triglycerides may continue telmisartan.

## **8.0 CRITERIA FOR DISCONTINUATION**

### **8.1 Permanent Study Drug Discontinuation**

Study drug discontinuation can occur for the following reasons:

- Drug-related toxicity requiring permanent discontinuation (see Sections 7.2, 7.3).
- Requirement for prohibited concomitant drugs (see Section 4.2.3).
- Request by subject to terminate treatment.
- Confirmation of virologic failure (two measurements of HIV RNA  $> 50$  copies/mL at least 2 weeks apart).
- Clinical reasons believed life-threatening by the physician, even if not addressed in the toxicity section of the protocol.
- Subject repeatedly noncompliant with telmisartan as prescribed.
- Subject discontinues telmisartan for  $\geq 14$  consecutive days.
- Failure by the subject to attend  $\geq 3$  consecutive clinic visits.
- Pregnancy or breast-feeding.

### **8.2 Premature Study Discontinuation**

- Request by the subject to withdraw.

- Request of the primary care provider if he or she thinks the study is no longer in the best interest of the subject.
- Subject judged by the investigator to be at significant risk of causing harm to self.
- At the discretion of the IRB, Food and Drug Administration (FDA), Office for Human Research Protections (OHRP), investigator, or the pharmaceutical sponsor.

### **8.3 Early Discontinuation**

Any subject who develops a Grade 3 or 4 symptom or laboratory abnormality (other than cholesterol, and triglycerides), UNLESS THE INVESTIGATOR HAS A COMPELLING REASON TO THINK IT IS NOT RELATED TO TELMISARTAN) will be evaluated and will have study treatment withheld until the toxicity resolves ( $\leq$  grade 2). If the abnormality is thought to be related to study treatment, the subject will not be re-challenged without discussion with protocol chairs (see Sections 7.2, 7.3). Subjects requiring premature study discontinuation will undergo a final safety evaluation and CT scan. Serum and plasma will also be banked at the time of study discontinuation (in lieu of the Week 12 or Week 24 sample). All subjects will remain in follow-up for resolution of Grade 3 or 4 toxicities.

## **9.0 SAMPLE SIZE AND ENDPOINTS**

### **9.1 Sample Size**

In a recently reported study of growth hormone releasing factor in HIV lipodystrophy, the FDA determined an 8% change in visceral abdominal fat between the active and placebo arms would define a clinically meaningful difference in VAT volume, assuming a standard deviation of 18.5%. However, we will aim for 10% difference in visceral fat to make it more clinically significant.

Using the parameters recommended by the FDA, we estimate that a sample size of 27 subjects will provide 80% power to detect a 10% reduction in VAT over 24 weeks in subjects treated with telmisartan (two-sided alpha level=0.05). We have increased the sample size to 35 subjects to improve our power to look at secondary endpoints, and to account for potential loss of follow-up. The total sample size is 35 subjects.

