## 9.6 Analyses

All statistical tests will be two-sided with nominal level of 0.05. Analysis will be exploratory without adjusting for multiple testing.

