### 9.6.1 Primary Analysis

Comparison of VAT volume change between Weeks 0 and 24 will be assessed using the paired t test. The primary analysis will be as-treated, excluding subjects who do not remain on the study regimen and/or subjects who do not have an observed primary endpoint. Subjects who discontinue telmisartan for  $\geq 14$  consecutive days will not contribute to the primary outcome after the date they first discontinued medication. An intent-to-treat analysis will be performed as a supplement.

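### Section 9.1's reason for planning on 10% instead of 8% is wrong: it only lowers the required number, and the paired t test can be significant at an observed reduction below both figures

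*Protocol*

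**What the plan says.** Section 9.1 takes its benchmark from a placebo-controlled study of another agent, where "the FDA determined an 8% change in visceral abdominal fat between the active and placebo arms would define a clinically meaningful difference", "assuming a standard deviation of 18.5" percent. It then departs from that benchmark: "we will aim for 10% difference in visceral fat to make it more clinically significant". On this basis "we estimate that a sample size of 27 subjects will provide 80% power to detect a 10% reduction in VAT over 24 weeks", with "two-sided alpha level=0.05". Enrolment is set at 35, to help with secondary endpoints and to cover loss to follow-up.

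The hypothesis in section 1.1 is a 10% reduction in VAT over 24 weeks. Section 9.6.1 gives the test: "Comparison of VAT volume change between Weeks 0 and 24 will be assessed using the paired t test". That analysis is as-treated and leaves out subjects who go off the regimen or have no observed endpoint. Section 9.6 adds "All statistical tests will be two-sided with nominal level of 0.05" and calls the analysis exploratory. Sections 3.0 and 9.2 describe a single-arm, open-label pilot.

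**The concern.** The sentence that sets the 10% target treats the planning effect as if it were a bar that the result must clear. It is not. The planning effect enters only the sample size formula, and a larger value gives a smaller trial. What the trial can conclude depends on the test, and a paired t test asks only whether the mean change differs from zero.

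This matters because the hypothesis is itself stated as a 10% reduction, and section 9.1 tells the reader that aiming for 10% adds clinical weight. Together they invite p<0.05 to be read as confirmation of a 10% reduction, or at least of a clinically meaningful one. The test shows neither. The 8% benchmark is also a difference between arms, while this trial measures change from baseline without a control, and the protocol does not comment on the mismatch.

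A smaller matter is that the stated 80% belongs to a normal approximation, not to the t test that section 9.6.1 names.

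**Working it through.** **Inputs.** From section 9.1: effects 10% and 8%, SD 18.5%, power 80%, two-sided alpha 0.05, 27 needed, 35 enrolled. From section 9.6.1: paired t test.

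**Assumption.** 18.5% is the SD of the within-subject percent change. Section 9.1 does not say so, but this reading reproduces its number.

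**1. The plan's own figure.** Normal formula for one sample of paired changes, n = ((1.960 + 0.842) × SD / effect)²:

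- Effect 10%: (2.802 × 18.5 / 10)² = 26.86, rounded up to 27. Power at 27 is 80.2% by the same approximation. The stated figure reproduces.
- Effect 8%: (2.802 × 18.5 / 8)² = 41.97, rounded up to 42.

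Moving from 8% to 10% therefore cuts the requirement from 42 to 27.

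**2. The planned test.** Noncentral t with n − 1 degrees of freedom, noncentrality = effect × √n / 18.5. At n = 27 and 10% the noncentrality is 2.81 and the critical value 2.056.

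| Evaluable n | Power at true 10% | Power at true 8% |
|---|---|---|
| 27 | 77.2% | 58.1% |
| 29 | 80.2% | 61.4% |
| 35 | 87.4% | 70.0% |

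For 80% power the t test needs 29 at 10% and 44 at 8%. The number that can be lost from 35 while keeping 80% power at 10% is 35 − 29 = 6 (17%), not 35 − 27 = 8 (23%).

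**3. Smallest observed mean reduction that is significant.** t(0.975, n − 1) × 18.5 / √n:

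- n = 35: 2.032 × 3.127 = 6.4%.
- n = 27: 2.056 × 3.560 = 7.3%.

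Both are below 8% and 10%. The same quantities are the half-widths of the 95% CI.

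**4. What the interval would show.** With 35 evaluable, an observed 6.4% has an interval from about 0 to 12.8%. An observed 10% has one from 3.6% to 16.4%. The first is significant without establishing 8% or 10%. The second matches the hypothesis in its estimate, yet does not exclude reductions well below 8%.

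**5. Sensitivity to the SD.** At n = 27 and a 10% effect, t-test power is 81.5% at SD 17.5%, 79.4% at 18.0%, 77.2% at 18.5% and 74.9% at 19.0%. An SD of about 17.85% would give 80%.

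**The case against.** The case for leaving section 9.1 alone has real substance.

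- **The sample size is not miscalculated.** 27 with 80% is a correct result of a standard formula, offered as an estimate. The t test asks for two more subjects, and 35 are enrolled, where power for 10% is 87%. This stands. A reader might infer that the trial is underpowered for its own target. The documents do not support that: power falls below 80% only if more than 6 of 35 are lost, and no expected loss rate is given. The gap between 77% and 80% is also smaller than the effect of a modest change in the SD.
- **Power at 8% is not misstated.** A reader might take 58% to 70% as contradicting the plan. The protocol claims no power at 8%; it openly sizes for 10%, in line with section 1.1. Lower power at a smaller effect is a consequence of that choice. Moreover, the 8% is a between-arm figure, so it cannot be used as an exact yardstick for a within-subject change, by the protocol or by its critics.
- **Any test against zero reaches significance below its planning effect.** True, and the protocol does not say that p<0.05 establishes 8% or 10%. The study is also a pilot with exploratory analysis, and details of reporting may sit in a SAP that is not shown.

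The last argument does not rescue the stated rationale. Section 9.1 itself claims that planning on 10% adds clinical significance, and that claim is false whatever a SAP contains. Because every such test behaves this way, choosing a larger planning effect cannot deliver what the sentence promises.

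**Conclusion.** The rationale in section 9.1 is wrong and should be corrected. Raising the planning effect from 8% to 10% reduces the required number by 15 under either method (42 to 27, or 44 to 29) and adds nothing to the clinical meaning of a positive result. A mean reduction of 6.4% with 35 evaluable subjects, or 7.3% with 27, would be significant, so p<0.05 alone cannot support the section 1.1 hypothesis.

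The difference between the normal approximation and the t test is minor: 2 subjects, or 2.8 points of power at 27. It is worth restating because it costs nothing and shrinks the loss allowance from 8 to 6.

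The arithmetic is certain given its inputs. It rests on 18.5% being the SD of within-subject percent change; between 17.5% and 19.0%, power at 27 runs from about 82% to 75%. The point about the rationale does not depend on the SD.

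**What to change.** Keep enrolment at 35 and change the wording.

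1. **Power statement in section 9.1.** Restate along these lines: 29 evaluable subjects give 80% power for a 10% change by paired t test (77% with 27, 87% with 35), taking 18.5% as the SD of within-subject percent change; power for a true 8% change is 58% with 27 and 70% with 35.
2. **Rationale.** Delete the clause that justifies the 10% target by clinical significance. State that 8% was a placebo-controlled, between-arm difference and so only an indirect reference for an uncontrolled change.
3. **Interpretation, in section 9.6.1.** State that p<0.05 will be reported only as a change from baseline, and that the 10% hypothesis will be judged from the estimated percent change with its 95% CI (expected half-width about 6.4 points with 35, 7.3 with 27). Section 9.6.1 speaks of volume change and objective 1.2.1 of a median change, so the text should say how the percent estimate relates to these.

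The cost is a slightly less favourable stated power and a loss allowance of 6 of 35 (17%) in place of 8 (23%). No procedure, visit or subject number changes.
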